**Methods:**

This trial implements a two-factorial, randomized, controlled, multi-arm, prospective, interventional, single-blinded design with cluster sampling and four study arms, each representing a different SARS-CoV-2 testing and surveillance strategy based on individuals’ self-collection of saliva samples which are then sent to and analyzed by a laboratory. The targeted sample size for the trial is 10,000 saliva samples equally allocated to the four study arms (2500 participants per arm). Strategies differ with respect to tested population groups (individuals vs. all household members) and testing approach (without vs. with pre-screening survey). The trial is complemented by an economic evaluation and qualitative assessment of user experiences. Primary outcomes include costs per completely screened person, costs per positive case, positive detection rate, and precision of positive detection rate.

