## Methods/design

### Study outcomes

Identification of the one best strategy will be determined by a series of parameters. Primary study outcomes include cost per correctly screened person (including costs related to contacting, pre-screening, and testing of participants); cost per positive symptomatic and asymptomatic case (including costs related to contacting, pre-screening, and testing of participants); positive detection rates (i.e., 4-week cumulative SARS-CoV-2 prevalence); and the precision of positive detection rates (i.e., confidence intervals of the estimators).

Further, secondary outcomes include the overall participation rate (i.e., number of participants for whom a test result—with and without pre-screening—is available out of the total number of contacted participants), costs per asymptomatic case, prevalence estimates, number of asymptomatic cases by strategy, ratio of symptomatic to asymptomatic cases by strategy, and participant satisfaction.

Lastly, the *CoV-Surv Study* includes additional study components, i.e., a cost-effectiveness analysis, a prognostic modeling, and a qualitative assessment of participant perception and experience, which will complement trial data with data from other sources to address the following tertiary outcomes: cost-effectiveness of each of the four active strategies compared to the status quo of passive surveillance, the development of a prognostic model to predict hospital utilization caused by SARS-CoV-2, time between test shipment and test application, and time between test shipment and test result, as well as the perception and preferences of persons in respect to being subjected to surveillance.

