#### Strategy B2

Individuals (one per household) receive information by mail on how to complete a brief pre-screening questionnaire which asks about COVID-19-related clinical symptoms. Only individuals whose pre-screening score crosses a defined threshold will then receive additional study material by mail with instructions on how to produce their own as well as saliva samples from each household member and how to return these samples by mail. Once received by the laboratory, the samples are tested for SARS-CoV-2 using RT-LAMP.

Of the four surveillance strategies, strategy A1 is considered the gold standard for prevalence estimation and thus used to determine the bias introduced by each of the other strategies. To determine the cost-effectiveness, each strategy is compared to a status quo, defined as the currently practiced passive surveillance approach. In each strategy, RT-LAMP-positive samples are additionally analyzed with real-time quantitative RT-PCR (RT-qPCR) in order to minimize the number of false positives.

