### Study materials

Participants are asked to provide a saliva sample in a testing tube after gargling with 5ml saline solution. This sample is shipped to the laboratory by mail and then analyzed for SARS-CoV-2 using the RT-LAMP test. All positive-tested samples undergo additional confirmation analysis using the RT-PCR test. Depending on the strategy, some participants first take part in an online pre-screening survey. This short survey contains between 10 and 15 questions assessing the presence of symptoms of an early SARS-CoV-2 infection. This survey also collects information on a participant’s socio-demographic background (i.e., education, employment, household size). Participants of the qualitative study component further take part in a qualitative survey or an interview with open-ended questions. Participation in this qualitative study will commence after an individual’s trial participation has been completed.

To estimate the cost of the four surveillance strategies, an activity-based micro-costing approach is used to prospectively estimate the average cost per case completely screened and per case detected for each strategy. Data on the resource consumption of all activities related to the implementation of the four strategies will be categorized as either start-up or implementation cost. For each activity, data on resource consumption for both capital cost items (e.g., building, equipment, and vehicles) and recurrent cost items (e.g., personnel, materials, and consumables) will be collected directly from respective trial records. Unit costs will be taken from secondary data sources, such as financial statements, invoices, and salary schedules.

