### Statistical analyses

The primary analysis will consist of an intent-to-treat (ITT) evaluation. Secondary analysis will include an estimation of the complier average causal effect using standard instrumental variables [20]. Here, the instrumental variable represents the initial random ITT assignment to the four strategies. The effects on continuous primary and secondary endpoints (e.g., cost per fully screened person, cost per confirmed positive case, cost per asymptomatic case, precision of prevalence) are measured using standard ordinary least square regression. For the effects on binary endpoints, we will use the modified Poisson model [21]. Effects on ordinal categorical endpoints (e.g., participant satisfaction measured on a Likert scale) are measured using an ordered logistic regression. All analyses will be adjusted for clustering of standard errors at the level of the randomization unit (i.e., municipalities). Primary analyses will not account for any baseline covariates; secondary analyses will account for the baseline covariates of age and sex.

In order to comprehensively identify the most cost-effective surveillance strategy, the aforementioned ITT analysis is complemented by a cost-effectiveness analysis evaluating the cost-effectiveness of the four surveillance strategies in relation to the status quo of having only passive surveillance. The cost-effectiveness analysis and underlying micro-costing study adopt a health system perspective to account for all costs incurred at the level of the health system, including the economic costs of all resources consumed in relation to the implementation and maintenance of the four active surveillance strategies, as well as the cost of the comparator (i.e., the passive surveillance system). All costs are measured as continuous variables for each individual. To determine the cost-effectiveness of each of the four surveillance strategies, costs and effects (measured as the number of cases detected) will be set into relation to those of the status quo. Incremental cost-effectiveness ratios (ICERs) are computed for each surveillance strategy in relation to the status quo. The strategy with the lowest ICER is considered as most cost-effective and will then be further appraised in conjunction with information on the prognostic models (described below) to orient decision making on the choice of the most suitable surveillance strategy to be implemented in routine practice.

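### Ordinary least squares is assigned to cost per case and precision of prevalence, which exist only per arm, and one wording of the screened-person denominator cannot be observed

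*Protocol article*

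**What the plan says.** **The model.** Statistical analyses lists the cost and precision endpoints as continuous and states that "cost per confirmed positive case, cost per asymptomatic case, precision of prevalence) are measured using standard ordinary least square regression". Standard errors are to be clustered by municipality. No unit of analysis is given for these endpoints.

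**The quantities.** Study materials sets the micro-costing aim as to "prospectively estimate the average cost per case completely screened and per case detected for each strategy". Study outcomes lists as a primary outcome "the precision of positive detection rates (i.e., confidence intervals of the estimators". At person level the protocol offers only the numerator: "All costs are measured as continuous variables for each individual".

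**The denominator.** The abstract reads "Primary outcomes include costs per completely screened person, costs per positive case, positive detection rate, and precision of positive detection rate". Study outcomes has "cost per correctly screened person (including costs related to contacting, pre-screening, and testing of participants". Statistical analyses refers to a *fully* screened person. None of the three terms is defined.

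**Verification.** The closing paragraph under Strategy B2 says that "RT-LAMP-positive samples are additionally analyzed with real-time quantitative RT-PCR (RT-qPCR) in order to minimize the number of false positives". Under Study-related processes, B1 participants who screen negative on the questionnaire receive no kit, and B2 sends kits only to household members who screen positive.

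**The concern.** A regression needs one outcome value per unit. A person has a cost, but no person has a cost per case or a confidence-interval width. The named model therefore answers a different question for these endpoints, or needs a unit that the protocol does not name.

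This is more than detail left to an analysis plan, because the protocol does name a method and the method does not fit its own definitions. An analyst following the text could report a contrast in mean cost per person under the label of cost per case.

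The word *correctly* adds a separate difficulty. It makes a primary outcome depend on true infection status in people whose status is never established.

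**Working it through.** 1. **Reproduce the plan's precision figures.** Inputs from Power calculation: n = 2,500, Agresti-Coull interval, prevalence 0.5% with ±0.35%, and 0.2% with ±0.25%. With X ~ Bin(2,500, p), compute the probability that the 95% half-width is within the stated margin.
   - p = 0.5%: the margin is met for X ≤ 18, probability 94.9% (stated 95%).
   - p = 0.2%: the margin is met for X ≤ 8, probability 93.2% (stated 93%).

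   Both reproduce. They also show that precision, as the protocol uses it, is a single function of the arm's positive count.

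2. **Individuals as the unit.** Least squares of individual cost on arm estimates mean cost per person in each arm. Cost per case is total arm cost divided by confirmed cases in the arm. The case count is not part of the regression, and interval width has no individual value. Clustering by municipality changes the standard errors, not the quantity estimated.

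3. **Arms as the unit.** Four values less four arm parameters leaves 0 residual degrees of freedom, hence no standard error.

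4. **Smaller cells as the unit.** The protocol specifies none. Expected A1 positives are 2,500 × 0.005 = 12.5, or 2,500 × 0.002 = 5. This assumes that every infected sample is detected and that 2,500 is the arm total over all batches.
   - *Municipality.* Assume 57 equal cells (56 district municipalities plus Heidelberg). Each has 2,500/57 ≈ 43.9 samples and 12.5/57 ≈ 0.22 positives. The chance of no case, and so of an undefined ratio, is 0.995^43.9 ≈ 80% (about 92% at 0.2%). In simulation, averaging only the defined cells gives about 42 samples per case against a true 1/0.005 = 200.
   - *Batch.* Three equal batches give 12.5/3 ≈ 4.2 positives each. The chance of none is 0.995^833.3 ≈ 1.5% at 0.5%, and 0.998^833.3 ≈ 19% at 0.2%.

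5. **Uncertainty of the ratio.** The coefficient of variation of the case count is about 1/√12.5 = 28%, or 1/√5 = 45%. The simulated central 95% range of A1 samples per case is 125 to 417 (true 200) at 0.5%, and 250 to 2,500 (true 500) at 0.2%. The random denominator cannot be ignored.

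6. **The screened-person denominator in B1.** Inputs from Power calculation: sensitivity 90%, specificity 70%, prevalence 0.5%, 3,125 kits, 2,500 samples.
   - Screen-positive share: 0.9 × 0.005 + 0.3 × 0.995 = 0.303.
   - Completers needed: 3,125/0.303 ≈ 10,313, as the protocol states.
   - Questionnaire-negative and untested: 10,313 − 3,125 = 7,188.
   - Infected but screened negative: 10,313 × 0.005 × 0.1 ≈ 5.
   - Denominator: 2,500 if only tested persons count; 7,188 + 2,500 = 9,688 if questionnaire-negatives also count. The ratio is 9,688/2,500 ≈ 3.9.

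   Whether those 7,188 people were screened correctly is never observed, nor is it for RT-LAMP negatives in any arm.

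**The case against.** The best defence is that the text fixes no unit, so it does not commit the trial to an impossible analysis. Four arms by three batches would give 12 values and 12 − 4 = 8 residual degrees of freedom, and at 0.5% prevalence few A1 batch cells would be empty. This stands as far as it goes: the 0 degrees of freedom apply to arm-level values only. But the batch analysis is not stated, and it weakens quickly at 0.2%.

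Several stronger readings are tempting and are not supported:

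- **A 400-fold error in cost per case.** A reader might divide 5,000 A1 addresses by 12.5 positives and conclude that the regression returns a value 400 times too small. That requires regressing among positives only, each carrying just their own cost. The protocol says neither, and it includes contacting, pre-screening and testing costs in the outcome.
- **Three of four primary outcomes invalid.** Comparing mean individual costs by least squares is standard. For cost per screened person the problem lies in the denominator's definition, not in the model.
- **Three conflicting denominators.** *Completely* and *fully* are naturally synonyms; only *correctly* conflicts.
- **The cost-effectiveness ranking fails.** The incremental ratios are computed per strategy from costs and cases detected, and do not use the regression. Equally, they compare each strategy with passive surveillance and so do not supply the missing contrasts between arms.

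It is also fair that a fuller protocol or analysis plan may define who counts as screened. That does not cure a named model that misfits, or the word *correctly*.

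**Conclusion.** The point holds in this form. The named regression does not estimate two of the four primary outcomes (cost per positive case, precision of the detection rate) or one secondary outcome (cost per asymptomatic case) as the protocol defines them. No unit of analysis that would rescue it is stated.

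Separately, Study outcomes uses a denominator, *correctly* screened, that conflicts with the other sections and cannot be observed under the testing scheme described. Whether questionnaire-negatives count as screened changes B1's denominator about 3.9-fold.

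The conclusion about the model rests on the protocol's own definitions. The sparsity figures rest on its prevalence assumptions and on equal cells, which are illustrative. The B1 figures rest on its assumed pre-screening accuracy and response.

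**What to change.** - **Cost per case.** Estimate each cost-per-case outcome as a ratio of arm totals over all allocated addresses: total cost divided by confirmed cases, or by asymptomatic cases for the secondary outcome.
- **Intervals and arm contrasts.** Use a bootstrap that resamples primary sampling units within batch in the Rhein-Neckar District, and addresses or households within batch in Heidelberg. Fieller or delta-method intervals with the same clustering would also serve. Resampling households alone in the district would ignore the two-stage design and tend to understate uncertainty. State in advance how a resample with no case is handled.
- **Precision.** Report the design-based interval width for each arm, and compare arms with the same bootstrap.
- **Wording.** Replace *correctly* with *completely* screened in Study outcomes and use that term throughout. Report cost per screened person both with and without questionnaire-negatives in the denominator, since either definition is a choice.

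The cost is revised analysis wording and routine programming, with no new data. Intervals may be wider than the regression would have suggested.

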### Significance of study

Findings of the *CoV-Surv Study* will inform the choice of the most effective, acceptable, and cost-effective strategy for SARS-CoV-2 screening and testing, with the most effective and cost-effective strategy expected to be incorporated into the local public health department’s routine health surveillance activities. Additional investigation of its everyday performance will provide insight in the strategy’s applicability to real-time prevalence prediction and the usefulness of the resulting information for local policy makers to implement countermeasures to effectively prevent future nationwide lockdowns.

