For strategy A1, a response rate of 50% is assumed after one-time prompting, warranting a gross sample of at least 5000 addresses per batch; for strategy A2, an average household size of two with a response rate of 50% after prompting is assumed, warranting a gross sample of at least 2500 addresses per batch [24]. For strategy B1, a 50% response to the first letter and a 50% response to prompting is assumed; further, a response rate of 80% is assumed for those participating in the pre-screening with positive screening results. To ensure a total of 2500 tested samples, at least 3125 test kits must be mailed out for this strategy. Assuming the pre-screening tool’s sensitivity at 90% and specificity at 70% and given a SARS-CoV-2 prevalence of 0.5%, at least 10,313 (=3125/0.303) participants have to complete the pre-screening. Further assuming a 50% response to the initial pre-screening tool and a 50% response after prompting warrants a gross sample of at least 13,750 addresses. Similar to above, for strategy B2 an average household size of two members is assumed, which warrants a gross sample of at least 6875 addresses. For the entire trial, a minimum gross sample of 28,125 addresses is required.

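### Labelling the strategy with the lowest ICER against passive surveillance as most cost-effective is not a valid rule for choosing one of four strategies, and it can mislead if pre-screening misses many carriers

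*Protocol article*

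**What the plan says.** Under Statistical analyses, the protocol article gives every strategy the same comparator: "Incremental cost-effectiveness ratios (ICERs) are computed for each surveillance strategy in relation to the status quo". The effect is a count of detected cases: "costs and effects (measured as the number of cases detected) will be set into relation to those of the status quo". The rule follows: "The strategy with the lowest ICER is considered as most cost-effective". The same sentence sends that strategy on to an appraisal together with the prognostic models, the purpose being "to orient decision making on the choice of the most suitable surveillance strategy to be implemented in routine practice".

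Study outcomes makes clear that the options exclude one another: "Identification of the one best strategy will be determined by a series of parameters". The same section places cost-effectiveness against passive surveillance among the tertiary outcomes. The section Significance of study describes the intended use: "with the most effective and cost-effective strategy expected to be incorporated into the local public health department".

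The rule as written contains no comparison of one active strategy with another, no dominance step and no value per detected case.

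**The concern.** When only one of several programmes can be adopted, the question is what the additional cases cost on moving from one programme to the next more effective one, and whether that price is worth paying. A ratio against a common comparator does not answer this, because it discards the size of the effect. A strategy that finds more cases at a somewhat higher average cost can never be called most cost-effective under this rule, even if the extra cases are cheap relative to their value.

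Negative ratios, if any occur, cannot be ranked either. Saving EUR 5,000 with 10 extra cases gives -500. Saving EUR 5,000 with 50 extra cases gives -100, so the rule prefers the worse result. An option that costs EUR 1,000 more and finds 10 fewer cases also gives -100.

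At stake is which strategy goes forward, with the label of most cost-effective, to the appraisal that guides routine use.

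**Working it through.** **Inputs from the article (Power calculation).** Prevalence is 0.5%, half of it asymptomatic. Pre-screen sensitivity is 90% and specificity 70%. Response is 50% in A1 and A2. Pre-screening response is 50% plus half of the remainder, so 75%, in B1 and B2. Kit return after a positive pre-screen is 80%. Household size is 2 in A2 and B2.

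**The plan's own figure.** P(screen positive) = 0.005 × 0.9 + 0.995 × 0.3 = 0.303. Kits = 2500/0.8 = 3125. Completers = 3125/0.303 ≈ 10,313. Addresses ≈ 10,313/0.75 ≈ 13,750 for B1, and half of that, 6875, for B2. The total 5000 + 2500 + 13,750 + 6875 = 28,125 reproduces, so these yields are the plan's.

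**Assumptions of this check.** The article gives no unit costs for the RT-LAMP strategies. I take EUR 20 per mailed kit (in the A arms this covers the letter) and EUR 2 per letter or survey in the B arms. Two kits are mailed per A2 address. In B2 each household member is pre-screened, as Study-related processes describes. Costs and cases count as additions to passive surveillance, and the laboratory test is treated as error-free.

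**Cases at 90% sensitivity, per 10,000 addresses.**
- A1: 10,000 × 0.5 × 0.005 = 25
- A2: twice that, 50
- B1: 10,000 × 0.75 × 0.005 × 0.9 × 0.8 = 27
- B2: twice that, 54

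B2 finds the most cases. It also had the lowest ratio in all 24 combinations of assumed costs tried (letter EUR 1 to 4, kit EUR 3 to 6, test EUR 5 to 40). Here the rule gives the right answer.

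**Where this changes.** Per 10,000 addresses B2 finds 10,000 × 2 × 0.75 × 0.8 × 0.005 × Se = 60 × Se cases. This equals A2's 50 at Se = 50/60 = 83.3%. Below that, A2 finds more.

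**A plausible lower value.** Suppose the 90% holds for symptomatic carriers, while asymptomatic carriers are flagged only at the false-positive rate of 1 - 0.70 = 30%. Overall sensitivity is then 0.5 × 0.9 + 0.5 × 0.3 = 60%, and P(screen positive) = 0.005 × 0.6 + 0.995 × 0.3 = 0.3015. Per 100,000 addresses:

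| Strategy | Cost (EUR) | Cases | EUR per case |
|---|---|---|---|
| B1 | 200,000 + 75,000 × 0.3015 × 20 = 652,250 | 75,000 × 0.005 × 0.6 × 0.8 = 180 | 3,624 |
| A1 | 100,000 × 20 = 2,000,000 | 100,000 × 0.5 × 0.005 = 250 | 8,000 |
| B2 | 200,000 + 150,000 × 0.3015 × 20 = 1,104,500 | 150,000 × 0.005 × 0.6 × 0.8 = 360 | 3,068 |
| A2 | 200,000 × 20 = 4,000,000 | 100,000 × 0.5 × 2 × 0.005 = 500 | 8,000 |

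A1 is dominated by B2, which finds more cases for less money. B1 is extendedly dominated, since its ratio exceeds that of the more effective B2. The frontier is status quo, B2, A2.

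- Increment of A2 over B2: (4,000,000 - 1,104,500)/(500 - 360) = 2,895,500/140 ≈ EUR 20,700 per extra case.
- Net benefit at EUR 25,000 per case: B2 360 × 25,000 - 1,104,500 = 7,895,500; A2 500 × 25,000 - 4,000,000 = 8,500,000. A2 is better.
- Net benefit at EUR 15,000 per case: B2 4,295,500; A2 3,500,000. B2 is better.

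The lowest-ICER rule names B2 in both situations.

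**Sensitivity to the assumptions.** With letter, kit and test costed separately, the increment at 60% sensitivity is EUR 11,192 at 2/6/10, EUR 5,596 at 1/3/5 and EUR 24,868 at 4/6/40. Over the same cost sets it is EUR 9,786 to 43,482 at 70% sensitivity and EUR 39,119 to 173,788 at 80%.

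**Scale.** Now fix 2500 tests per strategy instead of addresses, at 60% sensitivity and EUR 20/2. A2 mails 5000 kits, costs EUR 100,000 and finds 2500 × 0.005 = 12.5 cases. B2 mails 3125 kits (EUR 62,500) and needs 3125/0.3015/0.75/2 ≈ 6,910 letters (EUR 13,820), about EUR 76,320 in all. It finds 2500 × 0.003/0.3015 ≈ 24.9 cases. B2 then beats A2 on both counts.

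**The case against.** The strongest reply is that the rule does no harm under the plan's own assumptions: at 90% sensitivity B2 is both the most effective per address and the lowest in ratio. The article also speaks of testing capacity as a constraint, and at equal numbers of tests B2 wins even at 60%. Both points stand. They limit when the rule misleads. They do not make it valid, because the trial is meant to find out the yields and costs and the rule must hold for whatever is observed. A lowest-ratio rule could be defended for divisible programmes that scale freely under a fixed budget, but the article does not argue this, and choosing one strategy for one region points the other way.

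A reader might infer several stronger things that the document does not support:
- That the rule alone settles what enters routine use. The lowest-ICER strategy is appraised further, and a series of parameters is to determine the best one. That appraisal is, however, described for the strategy already labelled, and it restores no missing comparison.
- That the rule always favours the smallest or cheapest programme. It favours the lowest average ratio. In the example it picks B2, which is larger and costlier than B1.
- That it wrongly sets A1 aside. In the example A1 is dominated by B2.
- That cases which passive surveillance finds anyway are counted as gain. Effects are to be set against those of the status quo, and nothing says that gross detections are used.
- That negative ratios are likely. Active testing is meant to supplement passive surveillance, so fewer detected cases than under passive surveillance alone is mainly a theoretical possibility.

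The absence of acceptability curves or bootstrap details is no fault in a condensed article.

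**Conclusion.** The concern holds in a limited form. The article positively states a rule that is not valid for choosing one of several mutually exclusive strategies, because it ignores the size of the effect and the value of a case. An error is possible, not certain. Per address contacted, a conflict between B2 and A2 arises only if pre-screen sensitivity over all carriers is below 83.3%. At 60% the rule still names B2, although A2 is preferable once an extra case is worth more than about EUR 20,700, or about EUR 5,600 to 24,900 under the other assumed costs. The unit costs and the 60% are assumptions, and mailing more than two kits per A2 address would raise that value. The preferred strategy also depends on whether addresses or tests are held equal, which the rule leaves open. The analysis is tertiary and informs the implementation choice without alone deciding it.

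**What to change.** Replace the lowest-ICER sentence with a full incremental analysis of the status quo and the four strategies:
- State one common scale, either per address contacted or per fixed testing capacity.
- Order the options by effect and remove those that are dominated or extendedly dominated.
- Report each remaining option's ICER against the next less effective remaining option.
- Judge by net benefit over a range of values per detected case, with its uncertainty.

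The planned cost and case data suffice, so completed recruitment is no obstacle. The price is a little more analysis work, and no single winner can be named without a stated value per case.
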